### Study setting

The study will be conducted in the cardiac intensive care unit at Boston Children’s Hospital, a quaternary referral center and standalone children’s hospital.

### Recruitment and study flow

Potential patients will be screened for eligibility, and one of the principal investigators will approach the family of an eligible patient for written consent. If the legal guardian grants consent, the patient will be enrolled in the study and then randomized to one of two arms. Please see consent form in Supplementary files. Study procedures will be continued until the patient (1) no longer requires respiratory support for greater than 24 h, (2) transfers to the floor or is discharged from the cardiac ICU, (3) completes 14 days of study drug, or (4) at any time during the study the primary provider believes that open-label acid suppression is indicated (Fig. 1). To ensure adequate enrollment and retention, we will provide education of the study objectives and procedures to important subspecialist groups, send mailers to eligible patients prior to delivery or surgery, and post signs about the study in the cardiac intensive care unit and preoperative clinic.

**Fig. 1 Fig1:**
[figure not shown]
Study flowchart of trial design

### Randomization

Eligible patients will be randomly assigned by Boston Children’s Research Pharmacy to receive either a histamine-2 receptor antagonist (i.e., ranitidine or famotidine per institutional standard) or placebo. The randomization assignments are generated by Boston Children’s Hospital’s proprietary randomization software, SciRan®. Randomization will be performed within 2 strata defined by admission type (medical or surgical) and age (neonate, age < 30 days, or infant, 1 month to 1 year). Allocation will be using permuted blocks in a 1:1 ratio to ensure balanced allocations across the two treatment groups within each stratum. Allocation concealment is achieved by ensuring that only the pharmacy team holds the randomization key. The pharmacy does not partake in the outcome variable assessment, and the study investigators do not have access to the randomization key.

### Sample size

We powered the precision of our feasibility estimates for both screening and drug initiation—which we deemed as the two most important feasibility measures. There are approximately 600 patients under 1 year of age admitted to the cardiac ICU each year, and we anticipate that an estimated 200 patients will be eligible over the 2-year recruitment period. The target to demonstrate feasibility is screening 80% of all patients. If *n* = 600, the lower limit of the 95% one-sided confidence interval will include 80% as long as the observed screening rate is at least 82.7%. There are 100 patients to be randomized in this pilot trial. The target to demonstrate feasibility with respect to drug initiation is to have 80% of randomized patients receive their first dose of study drug within 48 h. With *n* = 100, the lower limit of the 95% one-sided confidence interval will include 80% as long as the observed drug initiation rate is at least 86.9%. That is, as long as the observed drug initiation rate is at least 86.9%, we can be 95% confident that the drug initiation rate, to be realized in a future trial, is at least 80%. The study is not powered to assess a statistical difference between the incidence of UGI bleeding and hospital-acquired infections, as the historical incidences are very low, 0.5% and 2%, respectively. These outcomes will be further assessed in a future larger, multicenter trial.

For the assessment of oral, gastric, and stool microbiota, a total of 600 samples (2 samples per site) will be obtained from the 100 patients. We estimate detectable effect sizes using these sample sizes based on the Human Microbiome Project [14]. With adjustment for three covariates: one categorical binary (antibiotics), one continuous (age), and one categorical tertiary (hospital-acquired infections), we anticipate a power of 0.9 to detect a 1.36% level of rare taxon relative abundance and a 3.46% level of common taxa relative abundance, within a treatment arm between two time points, and similarly between two treatment arms at a given time point for either oral, gastric, or stool samples. All estimates incorporate stringent Bonferroni multiple-hypothesis correction to an adjusted *p* value of 0.05. Approximating as above, the corresponding detection limit for 250 metagenomic pathways with power of 0.9 would be 3.87%.

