### Outcomes

The central objective for our pilot study is to investigate whether a clinical trial assessing the safety and efficacy of withholding SUP in infants with CHD in the cardiac ICU is feasible. The trial will be considered feasible if each of the following 4 a priori variables are met: (1) > 80% of eligible patients are approached for consent (*screening*), (2) > 20% of eligible patients are randomized (*enrollment and consent*), (3) > 80% of consented patients received their first dose of study drug within 48 h (*allocation*), and (4) > 80% protocol compliance achieved (*protocol adherence*). Adherence to the protocol is defined as having received all doses of study drug as prescribed during the study period. Protocol deviation is defined as either premature termination of the study or prescription of SUP that is not part of the study while enrolled. In addition to feasibility, we will assess safety by comparing the difference in the incidence of clinically significant UGI bleeding and hospital-acquired infections between participants receiving SUP versus placebo. Finally, we will explore the changes to the gut microbiota by comparing the absolute and serial differences in the abundance of bacteria and functional microbial profiles between those receiving SUP compared to placebo. The study investigators will not be blinded to primary outcome measures. The microbiome specimens (for secondary outcome measure) will be processed and analyzed without revealing their study group allocation and thus will be blinded.

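### The 82.7% screening figure is worked out on 600 admissions, but the screening outcome is defined on about 200 eligible patients, for whom the matching figure is about 85%

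*Protocol article*

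**What the plan says.** The Sample size section of the protocol article names screening and drug initiation as its two most important feasibility measures and justifies the precision of each.

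**Screening.**
- It begins from "There are approximately 600 patients under 1 year of age admitted to the cardiac ICU each year" and adds that "we anticipate that an estimated 200 patients will be eligible over the 2-year recruitment period".
- It then states: "The target to demonstrate feasibility is screening 80% of all patients".
- The calculation opens with "If *n* = 600, the lower limit of the 95% one-sided confidence interval" and concludes that an observed rate of at least 82.7% is enough for a limit of 80%.
- The Outcomes section labels a different proportion as screening. The criterion is that more than "80% of eligible patients are approached for consent".

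**Drug initiation.**
- The Sample size section sets the target as "80% of randomized patients receive their first dose of study drug within" 48 h, with n = 100 and an observed rate of 86.9%.
- The Outcomes section applies the same 80% and 48 h to the share "of consented patients received their first dose of study drug within" that time.

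The Outcomes section calls the trial feasible only if all four criteria are met. The Feasibility analysis section promises a one-sided 95% confidence interval for each proportion.

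**The concern.** The number needed to bring a lower confidence limit up to 80% depends on the denominator: the fewer the patients, the higher the observed rate must be. The 82.7% belongs to 600 patients. The outcome that carries the name screening in the Outcomes section is expected to have about 200. Nor is 600 the number of admissions over the recruitment period, since it covers one of two years.

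Screening is one of the two measures on which the protocol rests its precision argument. Someone who later sees, say, 83% of eligible patients approached and compares it with the published 82.7% would conclude that the true rate is at least 80% with 95% confidence. With 200 patients that conclusion would be wrong.

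**Working it through.** **Inputs**, all from the Sample size and Outcomes sections: target 80%; one-sided 95% confidence; n = 600 (one year of admissions under 1 year of age); about 200 eligible patients over two years; n = 100 randomized; stated rates 82.7% and 86.9%. Two years of admissions is 2 × 600 = 1,200.

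**Method.** The exact (Clopper-Pearson) one-sided 95% lower limit for x successes in n is the 5th percentile of a Beta(x, n − x + 1) distribution. Set x = n·p and solve for the p at which this limit equals 0.80. Then find the smallest whole number of patients whose limit is at least 0.80.

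**Step 1: reproduce the stated figures.**
- n = 600: p = 82.74%, stated as 82.7%.
- n = 100: p = 86.89%, stated as 86.9%.

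One method reproduces both, so the arithmetic on the chosen denominators is correct.

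**Step 2: apply the same method to the other denominators.**

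| Denominator | n | Solved rate | First whole count | Limit at that count |
|---|---|---|---|---|
| Admissions, one year (as stated) | 600 | 82.7% | 497 (82.8%) | 80.1% |
| Eligible patients, two years | 200 | 84.8% | 170 (85.0%) | 80.2% |
| Admissions, two years | 1,200 | 81.9% | 984 (82.0%) | 80.1% |

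**Step 3: does the choice of interval matter?** The score method gives 0.80 + 1.645 × √(0.80 × 0.20 / n).
- n = 600: 0.80 + 1.645 × 0.01633 = 82.7%.
- n = 200: 0.80 + 1.645 × 0.02828 = 84.65%.

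At n = 200 the Wald interval gives 84.2% and the score interval with continuity correction 84.9%. Every method lies between 84.2% and 85.0%, above 82.7%.

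**Step 4: what 82.7% delivers with 200 patients.** 0.827 × 200 = 165.4, so the first count to reach it is 166 (83.0%). The one-sided 95% lower limit at 166/200 is 78.0% exact, 78.2% score and 78.6% Wald. All are below 80%.

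**Step 5: drug initiation.** No recalculation applies. The 86.9% is right for 100 randomized patients. The Recruitment and study flow section places randomization after consent, and Table 1 allows consent before study day 1 with allocation on day 1. The consented count can therefore exceed the randomized count, but the article does not say by how much.

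**The case against.** **The decision rule is elsewhere.** The feasibility rule in Outcomes is simply more than 80%. It asks for no confidence limit, and 82.7% appears only in a precision argument introduced with a conditional n. This stands. A reader might infer that the wrong denominator raises the chance of a false pass on screening from 5% to 16.6%, which is the probability of at least 166/200 when the true rate is exactly 80%. The documents do not support that: they contain no pass rule at 166/200 and set no 5% false-pass rate. Under the stated rule the chance of passing at a true 80% is about 47% with 200 patients (at least 161) and about 48% with 600 (at least 481), so the denominator hardly matters to it.

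**The analysis will correct itself.** The reported interval will presumably use the actual denominator, so the final report would show the right limit. That limits the harm, but the published planning figure would still be at odds with it.

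**Screening may mean checking all admissions.** Read alone, the Sample size section is consistent on this apart from using one year instead of two. On that reading the two-year figure is 81.9%, and 82.7% is slightly too high, not too low. This also stands, so the direction of the error depends on the reading. But the quantity would then not be the one Outcomes calls screening, and that outcome would have no precision justification at all.

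**Consented and randomized patients may coincide.** Consent is followed by randomization, so the gap may be small. A reader might infer that the choice of denominator would reverse the drug-initiation verdict. That requires an assumed gap for which the article gives no figure. The difference in wording is all that can be claimed. The article also gives no ground for saying when the 48 h should start.

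**Conclusion.** The concern holds as a mismatch between a stated precision figure and the outcome it is meant to support. It is not an arithmetic slip, since 82.7% is correct for n = 600. For screening as the Outcomes section defines it, the required observed rate is 84.8%, or 170/200 (85.0%) in whole patients, about 2 percentage points above the stated figure. At 166/200 the lower limit is 78.0%, so the claimed assurance of 80% fails. Under the all-admissions reading the figure would be 81.9%, so n = 600 fits neither two-year denominator.

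This rests on the protocol's own estimate of 200 eligible patients, and the required rate will move with the actual count. The more-than-80% criterion, the 100 patients to be randomized and the planned intervals are unaffected. The drug-initiation denominators also differ between the two sections, with no size that can be put on the difference. Severity is moderate: worth correcting, but not a fault that undermines the feasibility verdict.

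**What to change.** - **Screening.** Use eligible patients as the denominator in both the Sample size and Outcomes sections. Replace the n = 600 statement with one to this effect: with about 200 eligible patients, the one-sided 95% lower limit is at least 80% when at least 170/200 (85%) are approached.
- **If coverage of all admissions is also of interest,** name it as a separate quantity and base its precision on about 1,200 admissions over two years (81.9%).
- **Drug initiation.** Use one denominator in both sections. The n = 100 and 86.9% already rest on randomized patients, so choosing that group leaves the figure unchanged. Choosing consented patients would mean stating their expected number and recalculating.

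The cost is wording only. Enrolment, procedures and the feasibility criteria stay as they are, and the stated screening figure becomes slightly less favourable (82.7% to 85%).

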#### Microbiome analysis

Once the rRNA sequencing is completed, we will perform taxonomic profiling to identify distinct microbial lineages and then compare them to the published Greengenes, SILVA (for 16S), and UNITE (for ITS1) Reference Database [18–20]. The primary characteristics to be assessed between treatment arms are as follows: (a) within-sample and between-sample overall ecology of the microbial community, (b) absolute and relative abundance of microbial communities, and (c) pattern classification analysis to identify diversity [21]. We will then perform per-feature multivariable association analyses that estimate which microbiome attributes differ by treatment arm as well as between time points, while accounting for covariates, to identify how microbes are affected by outcomes in the presence of certain covariates [22–24]. We will adjust for delivery type (C-section vs. vaginal delivery), nutrition type (breast milk vs. formula), and antibiotics prescribed to the patient (not mother) as these are known confounders in the infant gut microbiome.

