## Discussion

The practice of routine acid suppressive therapy in infants admitted to the CICU must be examined. Rising concerns related to the adverse effects of acid suppression, particularly hospital-acquired infections, must be acknowledged and the indications for this therapy need to be revisited. Therefore, we have proposed a pilot feasibility trial to explore the safety of withholding SUP and examine the changes to the microbiome after exposure to SUP in this population. Our trial will highlight the mechanisms by which SUP impacts the microbial dysbiosis of the gut and its association with hospital-acquired infections. If withholding of SUP is deemed safe and associated with less disruption of the gut microbial profile, it could guide a significant change in practice in centers where this therapy is routinely prescribed.

Although considered the gold standard, there are several barriers to conducting high-quality randomized controlled trials in pediatric critical care. Included in these barriers are scarcity of research funding and failure to complete the trial due to difficulty with patient enrollment in the ICU environment [12]. Given these hurdles, large randomized controlled trials are sparse in pediatric critical care and several trials have been stopped early, most commonly due to futility [25, 26]. To address the challenges with timely completion of a trial, certain governing bodies explicitly recommend that feasibility and pilot studies be conducted prior to undertaking and funding larger randomized controlled trials [27]. At the conclusion of our feasibility trial, we will be able to identify important barriers and, if necessary, amend the study protocol in order to proceed with a larger randomized controlled trial in the future. If this pilot trial concludes that a larger trial is feasible, we plan to conduct a non-inferiority, multicenter randomized controlled trial in pediatric cardiac ICUs focusing on clinical outcomes shortly thereafter. We hypothesize that withholding SUP in critically ill infants with CHD does not increase the incidence of UGI bleeding and results in less disruption of the gut microbiota, possibly decreasing the incidence of hospital-acquired infections, compared to SUP therapy. The results of our study will potentially define appropriate indications for SUP in infants admitted to the CICU and illuminate the mechanistic relationship between microbial alterations and outcomes during critical illness.

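### The microbiome detection limits assume a covariate set, including an infection outcome, that differs from the set named for analysis, which itself omits the stratification factors

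*Protocol article*

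**What the plan says.** Three parts of the protocol article bear on the covariates for the microbiome comparison.

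- **Sample size.** The power is calculated "With adjustment for three covariates: one categorical binary (antibiotics), one continuous (age), and one categorical tertiary (hospital-acquired infections". On that basis the plan anticipates "a power of 0.9 to detect a 1.36% level of rare taxon relative abundance and a 3.46% level of common taxa relative abundance", and a limit of 3.87% for 250 metagenomic pathways at the same power.
- **Microbiome analysis.** The per-feature multivariable models are to be fitted "while accounting for covariates, to identify how microbes are affected by outcomes in the presence of certain covariates". The named covariates follow: "We will adjust for delivery type (C-section vs. vaginal delivery), nutrition type (breast milk vs. formula), and antibiotics prescribed to the patient (not mother".
- **Randomization.** "Randomization will be performed within 2 strata defined by admission type (medical or surgical) and age".

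Two further statements fix the status of hospital-acquired infection. In the Outcomes section it is compared between arms: "we will assess safety by comparing the difference in the incidence of clinically significant UGI bleeding and hospital-acquired infections". In the Discussion, the hypothesis is that withholding prophylaxis "results in less disruption of the gut microbiota, possibly decreasing the incidence of hospital-acquired infections, compared to SUP therapy".

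**The concern.** A detection limit is a property of a model. If the planning section and the analysis section name different models, the reader cannot tell what the secondary microbiome comparison is able to detect.

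Two choices of covariate also matter in themselves. Hospital-acquired infection occurs after allocation, is a trial outcome, and on the plan's own hypothesis lies downstream of both treatment and microbiota. Adjusting for it would remove any part of the arm effect associated with infection, so the estimate would no longer be the effect of randomized assignment. Conversely, age and admission type were thought important enough to stratify on, yet the analysis section names neither. When allocation is balanced on a prognostic factor that the model ignores, the arm estimate gains from the balance but the calculated standard error does not show it.

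Antibiotics and feeding raise a milder form of the first problem. The analysis section gives no time window for either, and Table 1 records both from study day 1 until 24 h after respiratory support ends. Exposure that begins after allocation cannot confound a randomized comparison, but it may be affected by treatment.

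**Working it through.** **1. The covariate lists side by side**

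| Factor | Sample size | Microbiome analysis | Stratifies randomization |
|---|---|---|---|
| Antibiotics | yes | yes | no |
| Age | yes | not named | yes |
| Hospital-acquired infection (3 levels) | yes | not named | no |
| Delivery type | no | yes | no |
| Nutrition type | no | yes | no |
| Admission type | no | not named | yes |

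One factor of six is common to the two models. Admission type is in neither.

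**2. The plan's own figures**

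The sample count reproduces: 100 patients × 3 sites × 2 samples = 600. The power of 0.9 can be neither confirmed nor refuted, because the article gives no standard deviation, no number of taxa tested and no variance explained by covariates. With an assumed 50 patients per arm and a two-sample normal formula, the implied standard deviation is

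SD = limit / [(z(1 − 0.05/(2m)) + z(0.9)) × √(2/50)], where m is the number of tests.

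- m = 1: the divisor is 0.648, so SD = 1.36/0.648 = 2.10 points (rare) and 3.46/0.648 = 5.34 points (common).
- m = 250: the divisor is 1.000, so SD = 1.36 and 3.46 points.
- m = 1000: the divisor is 1.067, so SD = 1.27 and 3.24 points.

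The limits are therefore compatible with a range of inputs. The finding is that they are tied to a different covariate set, not that they are numerically wrong.

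**3. How full the infection factor would be**

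The plan calls both safety outcomes rare, "as the historical incidences are very low, 0.5% and 2%, respectively", the second figure being for infection. With X ~ Binomial(100, 0.02):

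- E(X) = 100 × 0.02 = 2
- P(X = 0) = 0.98^100 = 0.133
- P(X ≤ 1) = 0.403
- P(X ≤ 2) = 0.677

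A three-level factor would often have an empty or single-patient level.

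**4. How much adjustment for infection would move the arm effect**

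This is an illustration. The assumed inputs, not in the article, are a direct arm effect of 0.5 SD and an infection effect of 1 SD. The total effect is 0.5 + 1 × (difference in infection rates), and adjustment returns the direct part. Simulation with 50 per arm gave:

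| Infection rates | Unadjusted | Adjusted |
|---|---|---|
| 2% vs 2% | 0.505 | 0.505 |
| 2% vs 10% | 0.577 | 0.498 |
| 10% vs 30% | 0.706 | 0.506 |

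At the plan's rate in both arms nothing moves. A gap appears only if infection is commoner than planned and differs between arms.

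**5. Omitted stratification factors**

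If these factors explain a share R² of the variance, the detectable difference without them is larger by 1/√(1 − R²). The article gives no R². For assumed values of 0.10, 0.20 and 0.30 the ratios are 1.054, 1.118 and 1.195, that is about 5% to 20% larger.

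**The case against.** The strongest reply is that the two harms cannot both arise from one model. If the analysis section governs, no named adjustment conditions on infection. If the Sample size section governs, age is included. That is right, and it limits the point. A reader might infer that the planned analysis will produce an arm effect biased by conditioning on infection. The documents do not support this: infection is a named covariate only in the power statement, and at 2% in both arms the shift is nil in the illustration.

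A second reply is that the analysis list need not be exhaustive. The text speaks of covariates in general before naming three, and a fuller analysis plan may add age and admission type. This also stands, so one cannot say that the powered model will certainly never be run. It does not reconcile the two printed lists, and admission type is in neither.

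Third, adjusting for patient antibiotics has a stated rationale, and it can be reasonable for changes over time within an arm. The caution here is about timing in the between-arm comparison. A reader might go further and attach a large percentage bias to on-study antibiotics, or a definite saving in patients to the stratification factors. Both would need inputs that the article does not give.

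Finally, the microbiome aim is secondary and exploratory, and the sample size rests on the precision of the feasibility estimates. That limits the consequences but leaves the mismatch in place.

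**Conclusion.** The point holds as an inconsistency with two poor covariate choices attached; it is not a demonstrated bias. The detection limits of 1.36%, 3.46% and 3.87% at power 0.9 are stated for a model that shares only antibiotics with the list named for analysis. That model includes a post-randomization outcome which, at the plan's 2%, about 2 of 100 patients would have. Its effect on the estimate is small at that rate, but it has no place in a treatment-effect model.

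The analysis list names neither stratification factor. Leaving them out makes standard errors too large to the extent that they predict the microbiome features. The size of that loss is unknown from the document; 5% to 20% on the detectable difference rests on an assumed R² of 0.10 to 0.30. The error is towards caution and does not invalidate the comparison.

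**What to change.** Use one covariate set for the between-arm microbiome comparison, in both sections:

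- arm, age, admission type and delivery type;
- antibiotic exposure and feeding type as of study day 1 or earlier;
- the baseline sample value only where a baseline sample exists, since the Discussion warns that gastric fluid may be scarce and stools irregular.

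Drop hospital-acquired infection from the power model. If its association with the microbiota is of interest, report it as a separate descriptive analysis. Confine on-study antibiotics and feeding to a sensitivity analysis. Restate the detection limits for this model, giving the standard deviation and number of tests used. Settle this before allocation is unblinded.

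**Cost.** Age, admission type and the baseline value add about three degrees of freedom to the list in the analysis section; removing a three-level factor frees two in the power model. Table 1 marks no antibiotic exposure before study day 1, so exposure before the first dose may have to be abstracted from charts. The restated limits may differ slightly. The feasibility outcomes and the 100 patients do not change.

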### Sample analyses

For assessment of stool microbiota, sequence-based microbial community surveys of stool samples will be carried out by 16S rRNA gene-based sequencing in the Microbial Genomics and Transcriptomics Core at the Broad Institute. Their protocol targets the V4 window of the 16S rRNA gene and uses Illumina MiSeq system at the Broad Genomics Platform to produce on average 25,000 quality filtered, stitched paired-end reads per sample, representing the current state-of-the-art [17]. In addition, a higher resolution community survey and complementary functional survey of a subset of the stool samples (20%) will be obtained using metagenomic shotgun DNA sequencing, to be performed at the Broad Institute in the Broad Technology Labs and Genomics Platform. Metagenomic libraries will be constructed using the Nextera XT DNA library preparation kit (Illumina) and sequencing will be performed on an Illumina HiSeq 2000 to generate a minimum of 2 Gb of 101 nt paired-end reads.

For evaluation of oral and gastric microbiota, samples will be subjected to ribosomal DNA (rDNA) amplicon sequencing to characterize the composition of these microbiome communities. First, DNA will be extracted using a robust commercial extraction kit. Next, rDNA hypervariable regions of specific kingdoms will be amplified using universal primers. For bacteria, 16S V3V4 will be targeted using 5′-CCTACGGGNGGCWGCAG-3′ and 5′-GGACTACNVGGGTWTCTAAT-3′; for fungi, ITS1 is targeted using 5′-CTYGGTCATTTAGAGGAAGTAA-3′ and 5′-GCTGCGTTCTTCATCGATGC-3′. Specifically, Illumina adapter sequences and variable spacers are added 5′ upstream of these sequences to enable high-throughput multiplexed sequencing. The prepared amplicons will then be pooled and sequenced using Illumina Miseq 2 × 300 bp platform. Illumina raw reads will be de-multiplexed, quality trimmed, dereplicated and denoised, and finally mapped against established rDNA databases. The derived OTU table will document the relative abundance of each taxonomy within each sample.

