There are a few limitations we have identified in our current study protocol. First, the anticipated duration of respiratory support of more than 24 h was chosen as an enrollment criterion because it will exclude patients with short ICU stays and exposure to the intervention. To examine whether anticipated duration of respiratory support is a reasonable marker for length of stay and exposure to the intervention, we plan to compare actual duration of respiratory support and length of stay in those who screened in versus those who screened out. Second, obtaining gastric samples may be difficult in participants as infants often make very little gastric fluid when critically ill. Finally, some infants might not have regular bowel movements, limiting the frequency of stool samples and thereby limiting the longitudinal or treatment effect assessment.

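### The 3.87% detection limit at 0.9 power for metagenomic pathways does not account for shotgun sequencing of only 20% of stool samples

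*Protocol article*

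**What the plan says.** The Sample size section sets the base for the microbiome calculations: "a total of 600 samples (2 samples per site) will be obtained from the 100 patients". It continues: "We estimate detectable effect sizes using these sample sizes based on the Human Microbiome Project". For taxa it gives two limits: "we anticipate a power of 0.9 to detect a 1.36% level of rare taxon relative abundance and a 3.46% level of common taxa relative abundance". These apply within an arm between two time points, and between arms at one time point. On multiplicity: "All estimates incorporate stringent Bonferroni multiple-hypothesis correction to an adjusted *p* value of 0.05". The pathway figure follows: "Approximating as above, the corresponding detection limit for 250 metagenomic pathways with power of 0.9 would be 3.87" percent. No smaller sample number is attached to it.

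The Sample analyses section describes 16S sequencing for stool samples and amplicon sequencing for oral and gastric samples. Functional data come from elsewhere: a "complementary functional survey of a subset of the stool samples (20%) will be obtained using metagenomic shotgun DNA sequencing". The Sample size section does not mention this subset.

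The Abstract lists functional microbial profiles among the secondary outcomes. The Outcomes section describes the microbiota comparison as something to be explored.

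**The concern.** A detection limit depends on how many patients supply the measurement. The pathway limit is said to follow by the same approximation as the taxon limits, which rest on the full sample set, yet pathways are to be measured in one fifth of the stool samples. The published limit is only slightly above the common-taxa limit (3.87% against 3.46%), whereas a fivefold cut in sample number would by itself multiply a limit by √5 = 2.24.

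What is at stake is how a null pathway result will be read. Set against a published power of 0.9, it would suggest that acid suppression does not shift functional profiles by more than about 4 percentage points. If the comparison rests on about 10 infants per arm, it may support no such conclusion, and it could mislead the planning of the multicenter trial.

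**Working it through.** **Inputs from the article**
- Sample size: 100 patients, 2 samples per site, 600 samples in all; limits of 1.36% (rare taxa), 3.46% (common taxa) and 3.87% (250 pathways); power 0.9; Bonferroni correction to 0.05.
- Randomization: 1:1 allocation.
- Sample analyses: shotgun sequencing of 20% of stool samples.
- Not given: the standard deviation (SD), the number of taxa tested, sidedness, the number of shotgun samples, and their spread over patients, arms and time points.

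**Sample numbers**
- Full set: 600 / 3 sites = 200 stool samples; 100 patients / 2 arms = 50 per arm per time point.
- Subset: 0.20 × 200 = 40 samples. Taken as pairs, that is 20 patients, 10 per arm per time point.

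**Formula (normal approximation, two-sided)**

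Limit = SD × (z for α/2 + z for power) × √(2/n), with α = 0.05 / number of tests. For 250 pathways α = 0.0002, so the bracket is 3.719 + 1.282 = 5.001. Paired comparisons within an arm have the same 1/√n scaling.

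**Attempt to reproduce 3.87%**

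Without an SD the figure cannot be derived outright. It can be scaled from the 3.46% common-taxa limit, assuming the same SD and trying different numbers of taxa tested:

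| Taxa tested (assumed) | Pathway limit, all samples | Pathway limit, 20% of samples |
|---|---|---|
| 20 | 4.02% | 8.99% |
| 35 | 3.87% | 8.65% |
| 50 | 3.78% | 8.46% |
| 100 | 3.63% | 8.12% |
| 250 | 3.46% | 7.74% |
| 500 | 3.35% | 7.48% |

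The published figure fits the full sample set: about 35 taxa tested (two-sided), or about 41 (one-sided), gives 3.87%. With 20% of the samples and this SD, no number of taxa from 1 to 500 gives 3.87%; the two-sided limit runs from 11.9% down to 7.5%.

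**Limit for the subset**
- Same SD and same Bonferroni factor as common taxa: 3.46% / √0.2 = 7.74%.
- If 3.87% was the full-sample pathway limit: 3.87% / √0.2 = 8.65%, or about 8.7%.

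**Power for a 3.87% effect in the subset (two-sided)**
- If 3.87% was the full-sample limit: Φ(5.001 × √0.2 − 3.719) = Φ(−1.48) = 0.07.
- If the full-sample pathway limit was 3.46%: Φ(5.001 × 3.87 / 7.74 − 3.719) = Φ(−1.22) = 0.11.
- One-sided testing gives 0.08 and 0.13.

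With 10 per group and α = 0.0002 the normal approximation is, if anything, optimistic.

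**SD that would rescue the claim**

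For 3.87% to hold at power 0.9:
- 50 per arm: SD = 3.87 / (5.001 × √(2/50)) = 3.87 percentage points.
- 10 per arm: SD = 3.87 / (5.001 × √(2/10)) = 1.73 percentage points, smaller by a factor of 2.24.

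**The case against.** **The pathway SD is unknown.** The effect sizes come from an external data set, and pathways need not vary like common taxa. The article's own limits differ 2.5-fold between rare and common taxa at the same sample size. Scaled to 20% of samples they become 1.36% × 2.24 = 3.04% and 3.46% × 2.24 = 7.74%, and 3.87% lies between the two. This stands. It means that 7.7% is not a floor, and that a pathway SD of about 1.73 points would restore the claim. But the article does not say that pathways vary less; it says the figure follows by the same approximation.

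**The subset may exceed 40 samples.** Serial stool samples are planned (Measurements and definitions; Table 1), and the 20% applies to a total that is not fixed. At 8 to 10 stool samples per patient, 20% would be 160 to 200 samples. This stands as a reason to treat 40 as an assumption. The power statement, however, counts two samples per site. Repeat samples from one infant are correlated and add no patients to a comparison at one time point. The Discussion also warns that "some infants might not have regular bowel movements, limiting the frequency of stool samples".

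**A tempting inference: an 80%/20% slip.** Since (3.46 / 3.87)² = 0.80, a reader might infer that 80% of samples was entered in place of 20%. The documents do not show this. The match requires the same SD and the same number of tests for taxa and pathways, and the full sample with about 35 to 41 taxa fits equally well.

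**Incomplete sampling.** A reader might also want to discount the 16S limits, because "obtaining gastric samples may be difficult in participants" and stool may be infrequent. The Discussion already discloses both as possibilities, and no capture rate is given, so no size can be put on the effect.

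**Conclusion.** The point holds in a limited form. The stated limit and power for pathways do not account for the 20% shotgun subset, and the figures given do not allow them to be verified for it. Under the plain reading the limit is about 7.7% to 8.7% and power for a 3.87% effect is about 0.07 to 0.11. This rests on three assumptions: a pathway SD similar to that behind the common-taxa limit, two stool samples per patient, and a subset taken as pairs split evenly between arms.

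A reader might go further and conclude that power of 0.9 is impossible, or that the true limit is at least 7.7%. Neither follows without the pathway SD.

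Severity is minor to moderate. Functional profiles are a named secondary outcome, but the trial is sized on screening and drug initiation, and neither the feasibility outcomes nor the safety comparison uses this figure.

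**What to change.** Either of two changes is enough.

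1. Recompute the pathway limit for the subset. State how many patients and samples per arm and time point will be shotgun-sequenced and how they will be chosen. Give the SD, the number of tests and the sidedness behind the published figure, and restate the limit at power 0.9. If 3.87% already allows for the subset, say so and show the inputs.
2. Label the pathway analysis exploratory and remove the claim of 0.9 power for it.

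The cost is recalculation and wording. Enrolment, sampling and the sequencing budget are unchanged. Under the first option the published limit will probably become less favourable.
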